### CMR protocol

#### Basic description

For each patient, baseline and 1-year post-interventional CMR scans will be performed using standard protocols on a 1.5 T Siemens Aera scanner (at VUH) or a 1.5 T GE Discovery MR 450 scanner (at AAUH) with surface coils and prospective ECG triggering [3, 9]. Both sites will use corresponding CMR protocols. LV end-systolic and end-diastolic diameters, as well as maximal (end-diastolic) wall thickness, will be traced and recorded from the short-axis and long-axis views of the standard ECG-gated steady state-free precession cine sequence (8-mm slice thickness). LV volumes, mass, and ejection fraction will be measured using commercially available software (suiteHEART®, NeoSoft, USA or cmr42, Circle Cardiovascular Imaging Inc., Canada) from a stack of sequential 8-mm short axis slices (0–2-mm gap) from the atrio-ventricular ring to the apex. Measurements will be indexed to body surface area in m^2^ (using the DuBois and DuBois formula).

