#### LGE imaging

For detection of delayed hyperenhancement, images will be acquired 10–15 min after intravenous administration of Gadobutrol (0.2 mmol/kg) (Gadovist; Bayer AG, Germany) or Gadoteridol (0.2 mmol/kg) (Prohance; Bracco Imaging, Sweden) using a breath-hold segmented inversion recovery fast gradient echo sequence in the short-axis and long-axis planes of the LV, with an 8-mm slice thickness and 20% distance factor. The image parameters (VUH) are: repetition time of 700 ms, echo time 1.42 ms, flip angle 45°, matrix 256 × 184, and field of view 360 mm. For AAUH, the typical imaging parameters are as follows: repetition time 5.79 ms, echo time 2.72 ms, flip angle 15°, matrix 256 × 256, and field of view 380 mm. The optimal inversion time will be optimized for each patient to null normal myocardial signal, ranging from 220 to 320 ms (usually around 240 ms). The region of myocardial fibrosis will be defined as the sum of pixels with signal intensity above 5 standard deviations of the normal remote myocardium in each short-axis slice. The presence of myocardial fibrosis will be qualitatively determined by two independent readers, blinded to clinical data (2 radiologists with > 10 years of experience at VUH- [name] and [name], and 2 cardiologists with 8–10 years of experience at AAUH- [name] and [name]).

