#### T1 mapping

The present study describes image acquisition parameters by focusing on T1 mapping images, which will be acquired in four-chamber long-axis and short-axis (at the basal and midventricular levels) images before and at 15 min after contrast administration. All T1 mapping images have been acquired using modified Look-Locker inversion-recovery (MOLLI) [30, 31] using the Motion Correction technique (on the Siemens scanner). The following readout parameters will be used: slice thickness: 8 mm; flip angle: 35; field of view: 384 × 327; effective TI: 193 ms; voxel size: 1.5 × 1.5 × 8 mm; TR/TE: 312.64/1.33 ms; partial Fourier: 7/8; and parallel imaging factor: 2 (VUH) and slice thickness 8 mm, flip angle 35, matrix size 256 × 256, inversion time 130 ms, and FOV 380 mm (AAUH).

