#### Measurement of the ECV and native T1 values

The T1 maps will be generated from the CMR workstation after in-line motion correction just after image acquisition (Siemens scanner) or in post-processing software (GE scanner). Two blinded reviewers will independently review all T1 mapping sequences. Regions of interest will be drawn manually in the blood and septum at the midventricular level on the short-axis image, excluding the myocardium with LGE for T1 measurements [13, 32]. Regions of interest in the septum are chosen for myocardial T1, because this area corresponds to the site of myocardial biopsy. The regions of interest will be drawn on the compact myocardium, and the border of the myocardium will not be included. To measure the T1 value of blood, circular regions of interest will be positioned in the LV cavity, avoiding papillary muscle **(**Fig. 2**).**

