### Statistical analysis

Linear regression analysis to model the relationship between the extent of myocardial fibrosis and patient outcomes.Univariate and multivariate regression analysis of CMR-derived predictors of adverse clinical events.Comparison of clinical, serum, and imaging (CMR and echocardiography) biomarker data between patients with different extents of fibrosis.

The statistical analysis will be performed under the supervision of [name] at the Institute of Applied Mathematics, Vilnius University Faculty of Mathematics and Informatics. Descriptive statistics will be used to summarize the demographic, clinical, and imaging data characteristics of each patient. Categorical variables will be presented as the frequency and percentage, and continuous variables will be expressed as the mean and standard deviation or median and interquartile range. The 95% confidence interval will be reported for primary outcomes. Patients will be grouped, depending on the presence and extent of histologically measured myocardial fibrosis, and their clinical and imaging data will be compared for significant differences. Bivariate correlation analysis of the native T1, ECV, and GLS values with the degree of histologically measured myocardial fibrosis will be performed. Pearson or Spearman correlation coefficient will be used as the measure of correlation. To identify independent predictors of the degree of myocardial fibrosis, multivariate stepwise regression analysis will be performed separately for native T1, ECV, and GLS values, along with demographic and clinical data. The composite event will be assessed from a simple Cox model for survival analysis using ECV, native T1, and GLS, and their c-indexes will be compared for how well each marker predicts the clinical outcome. In addition, the Kaplan–Meier method will be used for the cumulative survival analysis with log-rank test to assess statistical differences between the curves of patients with different degree of myocardial fibrosis. A two-tailed *p*-value of < 0.05 will be considered statistically significant. The statistical analysis will be performed using the R language and environment for statistical computing (version 3.5.1) [37].

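### Native T1 (and, to a lesser degree, ECV) comes from two vendors' scanners, but the histology correlation and the simple Cox models with c-indexes contain no site term

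*Protocol article*

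**What the plan says.** All references are to the protocol article.

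- **Scanners (Basic description).** Scans are done "on a 1.5 T Siemens Aera scanner (at VUH) or a 1.5 T GE Discovery MR 450 scanner (at AAUH". The only statement on harmonisation is: "Both sites will use corresponding CMR protocols".
- **Mapping settings (T1 mapping).** Both sites use MOLLI, but the article gives motion correction only for one vendor: "using the Motion Correction technique (on the Siemens scanner". The effective TI at the Lithuanian site is 193 ms. The Danish settings end with "inversion time 130 ms, and FOV 380 mm (AAUH".
- **Map generation (Measurement of the ECV and native T1 values).** Maps come from "in-line motion correction just after image acquisition (Siemens scanner) or in post-processing software (GE scanner". The only agreement check described is between two observers in 10 patients. That measures readers, not scanners.
- **Analysis (Statistical analysis).** "Bivariate correlation analysis of the native T1, ECV, and GLS values with the degree of histologically measured myocardial fibrosis will be performed". For the composite event, a simple Cox model is planned with ECV, native T1 and GLS, and the markers' c-indexes are compared. Stepwise models use demographic and clinical data, without a covariate list.
- **Limitations.** Overlap of T1 values between normal and diseased myocardium is mentioned. Scanner and site differences are not.

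**The concern.** Native T1 is an absolute value in milliseconds. If one scanner reads systematically higher than the other, the pooled values carry a between-site component unrelated to fibrosis. A bivariate correlation and a one-marker Cox model cannot remove it. Three things are at stake:

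- **Dilution.** The offset acts like measurement error and shrinks the native T1 association with collagen volume fraction (CVF) and with outcome, even if the sites' patients are alike.
- **Confounding.** If fibrosis or event risk also differs by site, for instance through a different mix of surgical and transcatheter patients, the offset can create or distort an association.
- **An uneven comparison.** The c-indexes are meant to rank the markers. An offset would lower native T1's c-index for reasons that have nothing to do with its biological value.

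Validation against histology and prognosis are the study's two stated aims. About 60 surgical patients supply the biopsies, so the correlation has little precision to spare.

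**Working it through.** **The plan's own figure.** Sample size justification gives N = 100 for HR 1.32 per unit of ECV% with power 0.8. For a continuous covariate in a Cox model, N = (1.960 + 0.842)² / [ψ σ² (1 − ρ²) (ln HR)²], where ψ is the event proportion, σ the SD of ECV and ρ² the squared multiple correlation with the other covariates. The numerator is 7.849, and 7.849/(ln 1.32)² = 101.83. So N = 100 requires ψσ²(1 − ρ²) = 1.018. None of the three inputs is given, so 100 can be neither reproduced nor refuted. One set that fits is σ = 2.5, ρ² = 0 and ψ = 0.16. The section mentions no between-site variance, and the power applies to ECV%, not native T1.

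**Dilution of native T1.** The documents give no within-site SD, offset or site split. Assumptions: SD s = 40 ms, offset Δ = 20 to 60 ms, share p of patients at one site, and no true site difference in fibrosis or risk.

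- Attenuation of the log-HR: A = s² / (s² + p(1 − p)Δ²)
- Attenuation of the correlation: √A
- Power of a test that has 80% without an offset: Φ(√A × 2.802 − 1.960)

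| Split | Δ (ms) | A | √A | Power |
|---|---|---|---|---|
| 50/50 | 20 | 1600/1700 = 0.94 | 0.97 | 0.776 |
| 50/50 | 30 | 1600/1825 = 0.88 | 0.94 | 0.746 |
| 50/50 | 60 | 1600/2500 = 0.64 | 0.80 | 0.611 |
| 80/20 | 30 | 1600/1744 = 0.92 | 0.96 | 0.765 |
| 80/20 | 60 | 1600/2176 = 0.74 | 0.86 | 0.671 |

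Equal sites are the worst case, because p(1 − p) is largest there.

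**Confounding.** This was simulated with no within-site association, equal sites, and the offset in within-site SDs (1 SD = 40 ms above).

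| Scenario | Offset | False positives, no site term | With site handled |
|---|---|---|---|
| Correlation, n = 60; one site 0.5 SD higher in CVF | 1 SD | 13.6% | 4.5% |
| Same | 2 SD | 26.4% | 5.0% |
| Cox, N = 100, about 17 events; one site with twice the hazard | 1 SD | 10.8% | 6.3% |
| Same | 2 SD | 16.3% | 4.7% |

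Site was handled by a site term for the correlation and by a site term or stratification for the Cox model. The correlation used 4,000 runs per row and the Cox model 600. The Monte Carlo standard error at 10.8% is √(0.108 × 0.892/600), or about 1.3 points.

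**ECV.** ECV is (ΔR1 myocardium/ΔR1 blood) × (1 − haematocrit) × 100, with R1 = 1/T1. If a scanner multiplies every T1 by k, each ΔR1 is divided by k and the ratio is unchanged. An additive shift, or one that depends on the T1 level, does not cancel in full. So ECV has partial protection, of a degree that the documents do not allow one to quantify.

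**GLS.** Speckle tracking is analysed at the Lithuanian site only, so no site offset arises.

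**The case against.** The strongest reply has four parts.

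1. **A condensed article leaves detail to the analysis plan.** This stands for the multivariable models. Their covariates are not listed, and the sample size text refers to confounding covariates, so a site term there is not excluded. A reader might infer that no outcome model adjusts for site; the article does not support that. It does not answer the point for the bivariate correlation and the simple Cox model. Those are stated methods, and in that form neither contains site.
2. **No offset is shown.** This also stands. Both sites use 1.5 T, MOLLI, a flip angle of 35 and 8 mm slices, and the septal region-of-interest rule is common. The 193 ms and 130 ms figures carry different parameter labels, so their gap alone proves nothing. What remains is that vendor, settings and map generation differ, and nothing in the text would detect or remove an offset.
3. **Two contrast agents are allowed** ("Gadobutrol (0.2 mmol/kg) (Gadovist; Bayer AG, Germany) or Gadoteridol (0.2 mmol/kg) (Prohance; Bracco Imaging, Sweden"), and a reader might count this as a further site effect. It cannot affect native T1, which is measured before contrast. The agents are not tied to sites, so a site term would not necessarily correct their effect on ECV. Likewise, the two packages named under Basic description ("suiteHEART®, NeoSoft, USA or cmr42, Circle Cardiovascular Imaging Inc., Canada") are given for volumes, mass and ejection fraction, not for T1.
4. **Site adjustment discards information.** It removes any true difference in fibrosis between sites. That is a real cost, but the imaging values cannot separate such a difference from a scanner offset.

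**Conclusion.** The point holds for native T1, and to a lesser and unquantified degree for ECV, in the histology correlation and in the simple Cox models with their c-indexes. The plan should be changed, because protection is nearly free and the choice as written is exposed.

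The size is conditional. With a within-site SD of 40 ms and equal sites, an offset of 20 ms costs about 2 points from 80% power. Offsets of 30 to 60 ms lower power to about 75% to 61%, or about 77% to 67% at an 80/20 split. Confounding additionally requires a site difference in fibrosis or risk. In the examples it raises false positives from about 5% to between 11% and 26%, at offsets of 1 to 2 SD.

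Two stronger readings are not supported. The study's planned 80% power cannot be said to fall to these values, because it was calculated for ECV% and the table concerns a hypothetical native T1 test. Nor does every survival comparison need stratifying: the patient groups are described as histological, and if the log-rank groups are too, a scanner offset does not touch them.

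**What to change.** In Statistical analysis:

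- Replace the bivariate correlations of native T1 and ECV with CVF by site-adjusted (partial) correlations, Pearson or Spearman as already planned.
- Stratify the native T1 and ECV Cox models by site, and compute their c-indexes from within-site pairs.
- Report the unadjusted versions as a sensitivity analysis.
- State whether the log-rank groups are histological or defined by CMR values, and stratify by site only in the latter case.
- Leave the GLS analyses as they are.

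Within-site z-scores are not needed. Adjustment and stratification keep the millisecond and percentage scales.

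The cost is wording, since site is known for every patient and no new data are required. If the offset is negligible, little is lost. In the simulations with no offset and no site difference, power for a true correlation of 0.40 was 0.910 unadjusted and 0.905 adjusted, and Cox power was 0.79 either way. Restricting c-indexes to within-site pairs uses fewer pairs: a share p² + (1 − p)², which is 0.50 at an equal split and 0.68 at 80/20. Any true between-site difference in fibrosis is removed from the adjusted results, which is why the unadjusted ones should stand beside them.

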### Sample size justification

A sample size calculation was performed for the primary outcome: a composite of all-cause mortality and MACEs following AVR. To estimate the sample size required for the detection of a hazard ratio for ECV% of 1.32, R package powerSurvEpi was used [38]. Calculations were made assuming that the Cox proportional hazards regression model applies and taking into consideration a correlation of ECV% with other possible confounding covariates. On the basis of previous studies [15, 17] and assuming that the power of the test should be at least 0.8, a sample size of 100 patients is required. After an adjustment for 10% patient loss or withdrawal, a total sample size of 110 patients was selected. The selected sample size is comparable to other studies testing the association of myocardial fibrosis with adverse clinical outcomes.

### Study timetable

The ethics application was approved in March 2018. Study enrollment started in May 2019, and recruitment is expected to be completed in May 2021, with a further 24 months for follow-up, post-processing, and close-out of the study. The main study paper will be submitted within 6 months of the study close-out.

### Dissemination of results

The study results will be presented to the participating physicians and the general medical community. Following the complete data collection, the manuscript(s) based on the trial results will be submitted to peer-reviewed journals. Authorship criteria as defined by the International Committee of Medical Journal Editors will be followed.

## Discussion

FIB-AS is a study intended to investigate the role of multimodality imaging in the assessment of myocardial fibrosis in severe aortic stenosis patients and its prognostic significance in post-interventional outcomes. We sought to assess diffuse myocardial fibrosis by measuring the ECV and native T1 values obtained from CMR with T1 mapping and GLS from STE and to validate these results against the degree of myocardial fibrosis found from the histological examination. In addition, we will explore LV reverse remodeling following aortic valve intervention and its associations with patient clinical recovery. The results of the study will expand the current knowledge of cardiac remodeling in AS and will bring additional data on myocardial fibrosis and its clinical implications following AVR.

### Strengths

The present prospective multicenter study is designed to explore associations between left ventricular myocardial fibrosis and clinical outcomes in severe AS patients undergoing AVR. It has clearly established aims, inclusion and exclusion criteria, as well as defined methods and endpoints.The non-invasive measurement of myocardial fibrosis by CMR with T1 mapping is validated against invasive histological assessment.The trial is restricted to isolated AS, excluding cardiac pathologies which could possibly contribute to myocardial fibrosis burden, such as obstructive coronary heart disease and other significant valvular heart diseases.Inclusion of both surgical and TAVR cohorts will allow the investigation of patients with different risk profiles.

### Limitations

The selected sample size may be inadequate to allow a subgroup analysis.Limitations of CMR to establish diffuse and focal fibrosis: no reference regions of normal myocardium due to diffuse fibrosis, arbitrary selection of threshold of signal intensity, overlap of T1 values between normal and diseased myocardium.The FIB-AS study excludes patients with comorbidities, such as obstructive coronary artery disease, a history of myocardial infarction, renal failure, and persistent atrial arrhythmias; therefore, our results should not be overgeneralized to a broader AS patient population.

## Data Availability

Not applicable. Study patient enrollment and data collection is currently ongoing and no datasets were generated for analysis yet.

## Abbreviations

2D STE: Two-dimensional speckle tracking echocardiography
6MWT: 6-min walking test
AAUH: Aalborg University hospital
AS: Aortic stenosis
AVR: Aortic valve replacement
CAD: Coronary artery disease
CMR: Cardiovascular magnetic resonance
ECV: Extracellular volume
GLS: Global longitudinal strain
LGE: Late gadolinium enhancement
MOLLI: Modified look-locker inversion-recovery
NYHA: New York heart association
TAVR: Transcatheter aortic valve replacement
VUH: Vilnius University hospital
